## Abstract

**Background:**

Rupture of the anterior cruciate ligament (ACL) is common, especially in the active population. In defining the problem of ACL rehabilitation, this study draws from the knowledge that improved self-care, strength, and fitness are associated with better outcomes. Traditional rehabilitation involves regular physiotherapy, but it is not clear what the optimal way for delivering rehabilitation is, and it varies widely across the world. Evidence for treatments are discussed in the literature, however standard length of rehabilitation and frequency of appointments are unknown. Additionally, current rehabilitation models in the National Health Service (NHS) struggle with catering to large volumes of patients and the lengthy time span over which rehabilitation is delivered. The use of eHealth (the Internet in health care) has been successful at delivering behavior change to a number of diverse patient groups. In physiotherapy, problems such as exercise compliance, exercise technique, and managing a broad program of rehabilitation and advice can be challenging. An eHealth intervention called Taxonomy for the Rehabilitation of Knee Conditions (TRAK) to support self-management and behavior change has been developed by patients and clinicians, and acceptability studies have yielded positive results. TRAK is not an exercise rehabilitation protocol; it is a tool to support ACL rehabilitation with personalized plans, prompts, and logs to help adherence and videos and instructions to improve quality and address queries. The patients have their own log-ins and can email their physiotherapist through the website. This novel platform is directly in line with current NHS England, National Institute for Health and Care Excellence, and NHS Improvement agendas that call for rehabilitation initiatives using both technology and supported self-management for patients. This study forms part of a research platform to identify a best practice model of ACL care from the literature and opinions of key stakeholders. Patients’ exercise programs and duration of treatment are still based on individual needs, but use of the website may offer improved self-management and function and reduced health resource use.

**Objective:**

This is a feasibility study to establish recruitment, retention, sample size estimates, and practicality of collecting outcome measures to inform a future trial comparing the TRAK intervention, which has been rigorously designed to address the challenges of ACL rehabilitation, to usual care.

**Methods:**

This is a feasibility study comparing 2 groups: standard care and standard care plus eHealth. It will use convergent parallel mixed methods where both qualitative and quantitative data are sought for a more thorough understanding of the objectives. Primary outcomes relate to feasibility, including recruitment, retention, and usage. Secondary outcomes relate to health resource use and patient-rated outcome measures.

**Results:**

This research expects to establish the feasibility of a full-scale randomized controlled trial to explore whether patients who use an eHealth intervention to support ACL rehabilitation have better outcomes plus improved self-efficacy and reduced health resource use than a usual care group.

**Conclusions:**

The study will provide essential information to support the development and powering of a future clinical trial of eHealth and physiotherapy for patients with ACL reconstruction in the NHS.

## Introduction

### Background

Anterior cruciate ligament (ACL) rupture is a relatively common injury among those who are physically active [1-3]. Surgery is still the most common way to manage these patients and rehabilitation is essential [1-5] for “maximizing potential for patients to live a full and active life within their family, social networks, education/training and the workplace where appropriate” [5]. The optimal way for delivering rehabilitation is not clear, and current methods vary widely across the world [6-8]. Evidence for treatments is much discussed in the literature. This study addresses how current methods of service delivery in the National Health Service (NHS) struggle to cater to large volumes of patients and the lengthy time span over which rehabilitation is delivered [9-11]. Costing ACL rehabilitation in the NHS is not currently possible given that no standard guideline of care exists.

Some of the challenges of ACL rehabilitation include patient adherence, quality and type of exercises, motivation, and incomplete rehabilitation [3,4,6-8]. eHealth, defined as the use of the Internet in healthcare [12], could improve ACL rehabilitation when used as a tool to support behavior change and greater self-management [13,14]. To date, the use of eHealth has been successful at delivering behavior change to a number of diverse patient groups [12,15-17].

Taxonomy for the Rehabilitation of Knee Conditions (TRAK) is a website that targets behavior change to support self-management. It provides an individualized exercise program, progress log for key exercises, information section for each stage of rehabilitation, prompts, and videos and instructions to support the quality of rehabilitation [18] (see Multimedia Appendix 1). Patients log in to a personal account and have an embedded email link to the physiotherapist who oversees their program.

The TRAK intervention was developed at Cardiff University and has been the subject of a series of development studies to aid self-management in a cohort of patients with knee problems [10,19,20]. It is based on the TRAK ontology, which models standard care knee rehabilitation [20]. Further studies including an acceptability study of TRAK in an ACL population in the NHS are underway in a London hospital. TRAK is in line with current NHS England, National Institute for Health and Care Excellence (NICE), and NHS Improvement agendas and initiatives around rehabilitation using both increased technology and increased support for patients to self-manage [5,21,22].

### Objectives

A feasibility study is needed to establish recruitment, retention, sample size estimates and the practicality of collecting outcome measures. It will illuminate the mechanisms that may affect a future clinical trial comparing the TRAK intervention, which has been rigorously designed to address the behavioral challenges of ACL rehabilitation, to usual care.

## Methods

### A Mixed Methods Randomized Feasibility Trial

This study will use convergent parallel mixed methods where an embedded qualitative study will help expose the mechanisms influencing feasibility data such as recruitment, retention, and usage [23,24]. An online randomization tool will be used to mitigate imbalance between the arms and to assess whether it is possible to recruit to both arms of the study: standard care and standard care plus TRAK. This study will provide essential information to support the development and powering of a future clinical trial of eHealth and physiotherapy for patients with ACL reconstruction in the NHS.

The study will aim to recruit participants from the ACL rehabilitation pathway at a North London NHS Hospital. It will explore patient acceptance of the randomization process and of the burden of participation in a study such as submitting to demography profiling and outcome collection, attending training sessions and interviews, and committing to use the intervention [25-27].

Collecting information for an economic evaluation as part of research is important for potentially informing policy [25]. The study will assess the feasibility of collecting EQ-5D-5L, a validated outcome measure for health status which can be used for health and economic appraisal. It is used to calculate quality-adjusted life-years (QALYs) in a full trial to appraise health resource use in both arms of the study [28]. Descriptive statistics and data completeness for patient-completed health care resource use questionnaires will be reported. Methods, ease, and data completeness of collecting number and duration of physiotherapy appointments will be a particular focus of the work. This work will be supervised by a clinical trials unit health economist who will inform the feasibility trial procedures, including how data is captured and reported and how to deal with uncertainty in the data. 

A second part of the study will use semistructured interviews with patients and physiotherapists on their experiences of using TRAK. A schedule of questions will be used to provide an in-depth understanding of the user perspective of the intervention and the participation burden of the study that may have implications for a future trial. Conversations will be taped, transcribed verbatim, and analyzed using a thematic analysis discussed below.

### Selection Criteria

All adults immediately post ACL reconstruction who have been referred to the ACL rehabilitation program, are able to read and write English and give written informed consent, and have access to the Internet at home will be considered for this study. Individuals with complex comorbidities or surgeries such as multiligament reconstruction or fracture will be excluded from the study.

### Potential Ethical Considerations

Ethical approval will be sought from the Health Research Authority. There is a risk that using TRAK will not address an individual patient’s needs. The risk of this has been minimized by conducting a series of development research projects leading up to this study.

There is a risk that the participant’s symptoms deteriorate but remote monitoring through email will not identify this quickly. Since face-to-face treatment still applies and the patient can be identified when attending the group, this risk will be minimized. Patients will also be encouraged to air concerns with their therapist via email through the website.

There is a burden of time placed on the patient whereby they have to learn to use the website and take the time to log in daily. However, participants will have access to many aspects of TRAK beyond completion of the study through remote log-in, and using TRAK for some individuals will mean that rehabilitation can fit in better around their lifestyle.

### Consent

Treating clinicians will identify suitable participants when they attend the ACL group during their face-to-face consultation about their knee condition. If the individual is interested in finding out more about the study and gives verbal consent, the research team will be informed. All individuals will then speak to the lead applicant about the study and participation will be explained. The time of the lead applicant has been funded for this activity.

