Patient and public involvement (PPI) feedback that informed this application has indicated it is acceptable to randomize to either arm of the study. However, retention and usage data will show this more accurately and have significant implications on understanding of demand, implementation, and practicality of researching this new intervention in further studies.

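### Acceptability of randomisation is assigned to retention and usage data, which come only from patients who have already accepted it; refusals at the clinician step may also go uncounted

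*Protocol article*

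**What the plan says.** Acceptance of randomisation is a declared question. Under A Mixed Methods Randomized Feasibility Trial the article says: "It will explore patient acceptance of the randomization process". The paragraph on patient and public feedback that closes Sample Size reports that randomising to either arm was thought acceptable, and adds: "However, retention and usage data will show this more accurately".

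Sample Size also fixes the order of events: consent, then baseline measures, then randomisation. Usage is defined there by log-ins, email contacts and face-to-face attendance.

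The Consent section describes how patients reach the team. "Treating clinicians will identify suitable participants when they attend the ACL group during their face-to-face consultation about their knee condition". Then: "If the individual is interested in finding out more about the study and gives verbal consent, the research team will be informed". After that: "All individuals will then speak to the lead applicant about the study and participation will be explained".

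Recruitment is a primary outcome. The abstract says "Primary outcomes relate to feasibility, including recruitment, retention, and usage", and Primary Outcomes lists recruitment first. Neither place gives a numerator or denominator.

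The interviews are described as "semistructured interviews with patients and physiotherapists on their experiences of using TRAK", and are also meant to cover the burden of taking part.

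**The concern.** The article names a measure for acceptability of randomisation that cannot register the event of interest. A patient unwilling to be randomised does not consent, is not randomised, and contributes neither retention nor usage. High retention among those who agreed is compatible with many or few refusals beforehand.

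The referral route bears on the same question one step earlier. A patient who tells the clinician that they are not interested does not come to the research team by the route described. If nobody counts these patients, part of the refusal is lost, and a recruitment rate based on patients passed to the team would look better than uptake among all eligible patients. A future RCT needs that uptake figure, and the reasons behind it, to judge whether patients elsewhere would accept randomisation.

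**Working it through.** **1. Can retention and usage show refusal of randomisation?** Set the sections side by side.

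- Question (A Mixed Methods Randomized Feasibility Trial): do patients accept randomisation?
- Named evidence (end of Sample Size): retention and usage.
- Who contributes it (Sample Size): patients who have consented, completed baseline and been randomised.

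Every contributor has accepted randomisation, so the observed refusal rate in these data is zero by construction. Retention compared by arm can show dissatisfaction after allocation, which is a different quantity. Log-ins and other website activity exist only in the TRAK arm. Attendance exists in both arms, but Sample Size releases TRAK patients from weekly attendance and reads lower attendance as possible self-efficacy, so it is not a symmetric sign of accepting the allocation.

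**2. The article's own recruitment figures.**

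- New patients: 2 per week × 30 weeks = 60. Reproduced.
- With the additional pool: 60 + 15 = 75. Reproduced.
- Target: 2 × 35 = 70.
- Share needed: 70/75 = 93% of all potential recruits (Wilson 95% CI 85% to 97%), or 70/60 = 117% of the new patients alone.

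The target leaves little room for refusal, so uptake among all eligible patients matters.

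**3. Effect of the recruitment denominator.** Let q be the share of eligible patients who express interest to the clinician, and c the share of those who are then randomised.

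- Uptake over all eligible patients = q × c
- Uptake over interested patients only = c
- Overstatement factor = c/(q × c) = 1/q

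The article gives neither q nor c. Assuming 75 eligible patients and c = 0.80:

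| Assumed q | Rate over interested | Rate over eligible | Factor 1/q |
|---|---|---|---|
| 1.0 | 80% | 80% | 1.00 |
| 0.9 | 80% | 72% | 1.11 |
| 0.8 | 80% | 64% | 1.25 |
| 0.7 | 80% | 56% | 1.43 |
| 0.5 | 80% | 40% | 2.00 |

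For example, at q = 0.8, 75 × 0.8 = 60 are interested and 60 × 0.8 = 48 are randomised: 48/60 = 80%, but 48/75 = 64%. At q = 0.7, 42 are randomised and 42/75 = 56% (Wilson 95% CI 45% to 67%).

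If the rate is taken over the audit inflow of 60 or 75, the factor 1/q does not enter.

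**The case against.** Four points can be made for the plan, and each stands in part.

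First, the sentence in Sample Size contrasts panel opinion with trial data. It does not say that retention and usage are the only evidence, recruitment is a separate primary outcome, and retention by arm does bear on whether an allocation is tolerated. That is fair, but the sentence still names the wrong data for refusal, and no other section ties the question to refusal counts.

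Second, a reader might infer that the recruitment outcome is overstated. The article does not support this. It nowhere defines recruitment as a share of interested patients, and the only denominator it offers is the audit inflow. The bias is conditional. The audit figure is, however, a forecast from an average, of patients who may be eligible. It cannot separate patients who were ineligible, not approached, not interested or unwilling to be randomised.

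Third, a reader might infer that refusal is invisible. It is not: every patient passed on speaks to the lead applicant, so refusals at that point are seen. At the clinician step the article is silent on counting, and a screening log is a detail that an article may leave to the full protocol. Its absence is not itself an error. Nor does the phrase describing the interviews exclude usual-care patients, since the qualitative strand is also meant to explain recruitment and retention.

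Fourth, a reader might infer that the RCT would need more sites or time in proportion to 1/q. This does not follow. Sites and duration can be planned from patients randomised per week, which is fully observed. In the example above, 48/30 = 1.6 per week whichever denominator is used.

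**Conclusion.** The point holds in a limited form. The firm part needs no assumption: retention and usage arise after randomisation has been accepted, and website activity arises in one arm only, so they cannot answer the question of refusal that the article sets itself. A full protocol that kept the sentence would have the same fault.

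The second part is conditional. Refusals at the clinician step may go uncounted, and the recruitment rate may be overstated by 1/q, if clinicians keep no count and if the rate is taken over interested patients. The range of 1.11 to 2.0 rests on assumed q of 0.9 to 0.5; at q = 1, or over the audit inflow, there is no such inflation. The number randomised per week is unaffected.

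**What to change.** Replace the sentence at the end of Sample Size so that acceptability of randomisation is measured by the number of refusals among eligible patients and the reasons given, with refusal of randomisation as a separate category. Count them at both steps: with the treating clinician and after the talk with the lead applicant. Compare withdrawals and retention after allocation by arm as a supplement. Under Primary Outcomes, define recruitment as randomised/eligible, and report the weekly number randomised beside it.

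At the clinician step, an anonymous tally is enough: eligible, approached, interested, and reason if not. If the full protocol already has such a log, only the wording needs to change.

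The cost is a short tally sheet for clinicians at each group session over the 30 weeks. It should be in place before recruitment opens, because refusals not recorded at the time would be hard to recover. Interviewing some decliners is optional; it would need their agreement and approval, and the fix does not depend on it.

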### Sample Size 

Eligible and consenting patients will be recruited from a North London physiotherapy department. Patient recruitment will begin following completion of preliminary work packages on July 1, 2018. There are on average 2 new patients per week in the ACL group based on local audit data, which equates to 60 patients over 30 weeks who may be eligible for recruitment. There is potential for 15 further patients to be recruited from the first phase of rehabilitation bringing the potential recruits to 75 patients [29,30]. As the inclusion criteria are broad, it is expected that most patients will be eligible, and early patient feedback indicates patients will be keen to partake. Recruitment stops after 30 weeks, which allows the last recruited patient 7 months to participate. This is enough time to deliver on the study objectives of measuring feasibility although not necessarily enough time for patients to complete the program [30].

A sample size of 35 in each arm is recommended in feasibility studies in order to provide sufficient data and precision of means and variances to inform a future randomized controlled trial (RCT) [30]. Once patients have given consent, baseline measures will be collected. Each participant will then be randomized to either treatment or standard care group. This will be done through an online randomizing service. All will be given standard induction and then a TRAK induction for the intervention arm.

Retention will be measured by follow-up outcomes at markers of 6 weeks, 3 months, 6 months, and end of care or the trial. Usage of the website to determine uptake will be measured by the frequency of log-ins, email contacts, and attendance at face-to-face sessions. This will inform the retention rate and the engagement of patients with the intervention.

To assess the acceptability of the website as a self-management support tool, the patients in the TRAK arm of the study will not be obliged to attend weekly face-to-face sessions (although a minimum attendance will be stipulated). Attendance becomes a key measure of self-efficacy, where less face time may indicate greater self-efficacy and therefore informs the possibility of reduced face time for eHealth users in a future RCT. 

Patient and public involvement (PPI) feedback that informed this application has indicated it is acceptable to randomize to either arm of the study. However, retention and usage data will show this more accurately and have significant implications on understanding of demand, implementation, and practicality of researching this new intervention in further studies.

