### Arms of the Study

#### Treatment as Usual Group

ACL rehabilitation is an exercise group using evidence-based milestones to progress through a mix of strength and neuromuscular control exercises. Stages 1 and 2 are weekly, and stages 3 and 4 are every 2 weeks. Those who consent and are randomized to the usual care group will have a usual induction to the ACL rehab program, including

Recommended amount of exerciseTypes of exercise (personalised, related to goals)Appropriate use of ice, crutches, or bracing as individually indicatedEducation on potential red flags, expected milestones, and challenges of each stage

Patients will progress through the 4 phases of rehabilitation according to their ability. At each face-to-face session they will be assessed by their physiotherapist for quality of movement, strength, and neuromuscular control toward goal achievement.

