### Data Analysis and Frequency of Analysis

Standard procedures of data collection will be adhered to and guided by practices of the clinical trials unit. The qualitative and quantitative data strands are to be collected and analyzed simultaneously and with equal priority [23].

Quantitative data will be analyzed as follows: binary and other categorical measures will be summarized using frequencies and percentages and continuous measures using means and standard deviations (or medians and interquartile ranges for very skewed distributions). All outcome measures will be summarized separately by study arm. Differences in outcomes between arms will be estimated using multilevel linear or logistic regression models with a random effect of person to account for the repeated measures on individuals over time. Potential therapist effects will be appropriately modelled. The precision of estimates will be assessed using 95% confidence intervals. Power analyses will be conducted to calculate the sample size necessary to detect an effect of the intervention in a future RCT. 

The qualitative analysis will be done using a thematic analysis approach. This sees the data itself, rather than the theory, driving the process. The themes emerging from the interviews are grouped stringently so all the interview data relating to a particular theme are recorded. An explicit process of analysis will be outlined and reported, especially with regard to how data are weighted and reported secondary to frequency of occurrence or explanatory value [37]. The process will be largely inductive and will develop an epistemology of the ACL patient experience where preconceived ideas are suspended in favor of the unique perspectives of the participants. The patient’s “perception, thought, memory, imagination, and emotional experience of an event” is liberated and fully informs our understanding [38]. Interview data will be analyzed by the chief investigator and cross-checked by another supervisor.

Expected outputs:

Determining the feasibility of an RCT by gathering sufficient data to power a trial as outlinedDetermining the acceptability of TRAK as a tool of behavior change to physiotherapists and patients and illuminating the mechanisms that influence feasibility measuresDetermining the feasibility of gathering costing data to inform an economic analysis alongside a potential RCT

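### Attendance cannot be read as self-efficacy when only the TRAK arm is released from weekly sessions

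*Protocol article*

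**What the plan says.** All references are to the protocol article.

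- **Release of one arm (Sample Size).** To assess acceptability of the website, "the patients in the TRAK arm of the study will not be obliged to attend weekly face-to-face sessions". A minimum is to apply, but its value is not given.
- **Interpretation (Sample Size, next sentence).** "Attendance becomes a key measure of self-efficacy, where less face time may indicate greater self-efficacy". The sentence goes on to use this reading to inform whether eHealth users could have less face time in a later trial.
- **Usual care (Treatment as Usual Group).** "Stages 1 and 2 are weekly, and stages 3 and 4 are every 2 weeks". No release is stated.
- **Second use of attendance (Sample Size, preceding paragraph).** "Usage of the website to determine uptake will be measured by the frequency of log-ins, email contacts, and attendance at face-to-face sessions". On purpose: "This will inform the retention rate and the engagement of patients with the intervention".
- **Label of the contrast (abstract, Methods).** The study is described as "comparing 2 groups: standard care and standard care plus eHealth". The section A Mixed Methods Randomized Feasibility Trial names the arms in the same way, and the Intervention Group section does not mention the release.
- **Analysis (Data Analysis and Frequency of Analysis).** "Differences in outcomes between arms will be estimated using multilevel linear or logistic regression models".
- **Direct instrument (Secondary Outcomes).** The Stanford Self-Efficacy Questionnaire is already listed.

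**The concern.** A proxy for self-efficacy is informative between arms only if both arms face the same conditions for showing it. Here one arm may skip sessions and the other has no such permission. Randomization does not remove the problem, because the permission is part of what is randomized.

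The inference also has a practical destination: it is meant to feed the decision on reduced face time in the full trial. If the lower attendance came from permission or from patients drifting away, that later design would rest on a gain in self-efficacy that was never shown.

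The second use of attendance makes the reading less clear still. In one paragraph it sits with log-ins and emails as a sign of engagement; in the next, less of it is the favourable sign. Nothing in the article says how the two readings are to be kept apart.

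**Working it through.** No figure in the protocol bears on this point, so there is none to reproduce. The check is a comparison of passages and a short identification argument.

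**1. Attendance conditions by arm**

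| | TRAK arm | Usual care |
|---|---|---|
| Schedule | Weekly attendance not obligatory; a minimum of unstated value | Weekly in stages 1 and 2, two-weekly in stages 3 and 4 |
| Source | Sample Size | Treatment as Usual Group |

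The usual-care obligation is implied by its schedule, not spelled out. The asymmetry is nevertheless in the text, since only one arm is given a release.

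**2. What a between-arm difference contains**

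Let D be mean attendance in usual care minus mean attendance in the TRAK arm. Write

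D = R + T,

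where R is the part due to the release and T the part due to the website. Two arms give one D. Every split of D fits the data equally well, including R = D with T = 0. The multilevel model estimates D; it cannot divide it. D remains a valid randomized estimate of the package, TRAK plus its attendance rule.

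**3. What low attendance means for one patient**

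Three TRAK patients with the same low attendance:

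| Patient | Attendance | Log-ins and emails | Follow-up outcomes | Self-efficacy |
|---|---|---|---|---|
| Manages well alone | Low | Continue | Completed | Higher |
| Uses the permission for convenience | Low | Continue | Completed | Unchanged |
| Has disengaged | Low | Fall away | Likely missing | Unknown |

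Attendance does not distinguish the three. Log-ins and follow-up completion help to separate the third from the other two. Only a direct measure of self-efficacy separates the first from the second, and the Stanford questionnaire is that measure.

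**4. The two uses of attendance**

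As a component of usage and engagement, grouped with log-ins and email contacts, higher attendance naturally reads as better. As self-efficacy, lower attendance is said to be the better sign. The first direction is inferred from the grouping, because no scoring rule is written. Attendance at a physical session is, in any case, not use of a website.

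**5. The label of the arm**

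Standard care plus an addition implies that the standard-care component is the same in both arms. The release changes that component, so the abstract, the design section, the Sample Size section and the Intervention Group section do not give one consistent account of attendance in the TRAK arm.

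**The case against.** The other side has a good deal to say, and several stronger readings that a reader might infer do not hold.

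- **That the trial would show lower face time whatever TRAK does.** Not supported. The release is a permission, not an instruction; patients may still attend weekly, and attendance above the minimum is their choice. Lower attendance could follow from the rule; it need not.
- **That dropout is scored as success.** Not supported. Retention is measured separately, by follow-up outcomes at 6 weeks, 3 months, 6 months and the end of care or of the trial. Attendance only helps to inform it, and log-ins, emails and interviews give further information on engagement.
- **That attendance is formally scored in opposite directions.** No direction is written for usage, and the self-efficacy reading is hedged.
- **That face time is a primary efficacy outcome.** Face-to-face time and number of appointments do appear under Primary Outcomes, but they follow cost analysis and read naturally as its components. The abstract places health resource use among the secondary outcomes. The point does not depend on their status.
- **That a size can be put on the effect.** Assuming that patients skip some share of sessions and then reporting that face time falls by that share is circular.

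It is also fair to say that observing attendance when it is optional is a legitimate acceptability question within the TRAK arm, that no confirmatory test of attendance is planned, and that face-to-face assessment continues in that arm.

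None of this rescues the inference itself. The hedge is followed by a commitment: attendance is named a key measure, and its reading is carried forward to the next trial.

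**Conclusion.** The point stands in a limited form. Because the attendance rule differs by arm, a between-arm difference in attendance can be interpreted neither as self-efficacy nor as an effect of TRAK alone; the rule itself and disengagement are competing explanations. Listing the same variable as website usage adds an ambiguity, though not a written contradiction in scoring.

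No numerical size can be given, because the documents state neither the minimum attendance nor any expected attendance in either arm. The conclusion rests on one assumption: that usual-care patients are expected to follow their stated schedule. The consequence falls on the interpretation and on what is carried into the future trial. The target of 35 per arm is unaffected, and harm is limited by the self-efficacy questionnaire already in the plan. This is a statement the protocol makes wrongly, not a detail left to a fuller document.

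**What to change.** 1. Remove attendance as a measure of self-efficacy; use the Stanford Self-Efficacy Questionnaire for that purpose.
2. Report attendance, face-to-face time and number of appointments as resource use, labelled as observed under each arm's own attendance rule and read alongside log-ins and follow-up completion.
3. Remove attendance from the measures of website usage.
4. Reconcile the abstract, the design section, Sample Size and Intervention Group on the attendance rule of the TRAK arm, and state that the contrast estimates TRAK together with that rule. Which rule should apply is for the investigators.
5. Optionally, record the reason for absence.

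The cost is wording, plus one data field if the option is taken. The downside is a weaker claim: the study could report how much face time was used under the package, but not that less face time shows greater self-efficacy. The wording is best settled before recruitment starts.
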